### Recruitment

The participants are recruited from both inpatient and outpatient individuals at the Department of Psychiatry, Psychosomatics, and Psychotherapy at the University Hospital Frankfurt. Additionally, a physician collects data at the [name] Clinic in Königstein. For ongoing enrollment, patients will be screened regularly for participation criteria by the study teams and by their treating clinicians. Study information will be given by members of the study team who are not involved with the patient's treatment to prevent participation out of a sense of obligation and to maintain voluntary participation. There will be no assignment of interventions since participation does not include differing intervention types.

## Assignment of interventions: allocation

### Sequence generation

n/a: since participation comprises the recording of up to five regularly held therapy sessions and subsequent filling out of questionnaires which will be equally done by all study participants, sequence generation is not needed.

## Data collection and management

### Plans for assessment and collection of outcomes

The recording of the therapy sessions and the questionnaire data will be collected on the same day. An overview of all applied study instruments is depicted in Table 2. After giving the patient the study information and obtaining informed consent, audio recordings are conducted during routine medical activities. Up to five of their therapy sessions with a typical duration of 30–60 min are recorded. Audio recordings of therapeutic sessions are captured using high-quality recording equipment with carefully positioned microphones to minimize background noise and ensure clear speech capture. Recordings are made using a Tascam DR-40X audio recorder. Recordings are captured in stereo mode using the recorder's external left/right inputs. The audio is stored as uncompressed WAV files with a sampling rate of 48 kHz and a bit depth of 24 bit. The recorder input level is set to −12 dB, providing sufficient headroom to avoid clipping. Phantom power (48 V) is enabled to supply the external microphones. Audio signals are acquired using two external condenser microphones (the t.bone CC 75) with a frequency response of 20 Hz–20 kHz, corresponding to the standard human auditory range. Microphones are attached at the chest/collar area of the participants ensuring comparable distance to the mouth between the participants. Care is taken to ensure that the microphone grille did not come into contact with participants' clothing and is oriented toward the participant's head, in order to minimize clothing-rub noise and to enable more accurate recordings. These settings were chosen based on previous test runs using different setups of microphones and recording environments/parameters. We transcribed and diarized the recordings and manually evaluated the quality of these transcriptions with their corresponding audio recordings to find the best setup.

**Table 2 T2:** Overview of collected data.

Data category		Purpose of use	
Demographic data		Control of the study*’*s inclusion criteria	
Clinical data	Clinical Global Impression (CGI)	Dimensional measure of development of psychopathology	Assessment of the patient*’*s condition or psychopathology
	Clinical Global Impression of Suicide Severity (CGI-SS)		
	Global Assessment of Functioning (GAF)	Assessment of the general psychosocial functioning level	
	MiNi C Suicidality Scale (MiNi)	Assessment of suicide risk and preceded suicidality	
	Suicidality Scale of the Depressive Symptom Index (DSI-SS)	Measuring instrument for recording suicidality	
	Beck*’*s Depression Inventory (BDI- II)	Severity detection	
	Brief Psychiatric Rating Scale (BRPS)	Severity detection	
	Additional information obtained from medical record	Text based analysis	
	Medical history		
	Concomitant Medication		
Recording of the therapy sessions		Analysis of speech features	

Additionally, data on general psychosocial functioning and the severity of the patient's psychopathological state are collected using questionnaires completed by both therapists and patients.

The Clinical Global Impression (CGI) is a short assessment of the clinician's view of the patient's global functioning and to track patient progress or treatment response over time and comprises three measures of which we use two: severity of illness, global improvement, and an efficacy index (which we leave out) (48). The instrument has been proven to be a readily understood and practical measurement tool which is well applicable in the clinical practice (49) and has been used in different mental disorders including affective and psychotic disorders (50, 51). Additionally, we use the CGI-SS which is a modified version of the CGI to evaluate severity of and change in suicidality according to the version of Meltzer et al. (52). We only changed the time period from “past 7 days” to “since the last assessment”.

The Global Assessment of Functioning (GAF) scale is an established instrument for measuring illness severity in the clinical context and introduced as a rating scale within the DSM-III-R (53). The instrument has shown to be a valid and reliable measure of psychiatric illness (54).

### Plans to promote participant retention and complete follow-up

To promote retention of the participating patients and their therapists, we are integrating the participation progress in everyday clinical care with minimal extra effort for the participation process. If therapists or patients nevertheless want to end their participation, there will be no consequences or disadvantages.

### Data management

During the data collection phase, the raw audio recordings, patient data, and questionnaires will be collected. In this phase, only clinicians and student assistants from the University hospital in Frankfurt as well as one doctoral student from the Privatklinik [name] in Königstein are involved. The analysis of the data is conducted by the Ubiquitous Knowledge Processing (UKP) Lab at TU Darmstadt using natural language processing and multimodal methods and is mostly carried out in Darmstadt exclusively with pseudonymized data. The data accessed by the research group from TU Darmstadt will only have pseudonymized files and data without any personal information about the participants. The data analysis is complemented by a standardized assessment of the course by an independent board-certified psychiatrist or experienced assistant in psychiatry, serving as a “gold standard” for comparison with the AI analysis. Thus, the pseudonymized audio files are listened to and classified by a board-certified psychiatrist based on clinical features. The gold standard assessment covers three different areas. It consists of the BPRS as a broad psychopathology questionnaire, the five-stage severity item of the CGI-SS combined with an open question, asking the experts to briefly justify their rating within 2–3 sentences and the VTAS-R-Short Form, a five-item therapeutic alliance questionnaire (55).

The pseudonymized audio recordings will then be analyzed for acoustic and prosodic features using the open-source toolkit, openSMILE (56) and then transcribed to text with the freely available software WhisperX (57). Both datasets will then be analyzed on its own and later on fed to a multimodal neural network to generate a clinically relevant outcome score (e.g., suicidality prognosis score). Figure 1 shows an overview of our workflow.

**Figure 1 F1:**
[figure not shown]
Schematic depiction of data collection and analysis workflow.

Both, audio track and therapy transcript have to be pseudonymized to ensure data privacy. The sessions are transcribed to text with the freely available software WhisperX (57). In order to pseudonymize the data, the members of the study team listen to the therapy session and check the transcript at the same time. In this way it is not only possible to delete personal data but also keep track of transcription errors. Furthermore, this also enables the correction of errors in speaker diarization which will be relevant for data analysis. Transcripts are also edited according to predefined rules to ensure consistency, including standardized notation for stuttering and speech disfluencies, clear indication of overlapping speech, flagging of incomprehensible sections, and documentation of interruptions such as third parties entering. By doing this we are left with not only a pseudonymized audio track but also with a high quality pseudonymized and diarized transcript. Afterwards, the transcripts are ready for use with e.g., locally operating LLMs to assess their capability to distinguish between patient groups and evaluate symptom severity. The audio tracks are ready for feature extraction with the open-source toolkit openSMILE (56). Extracted audio features will serve as the basis for subsequent calculations, e.g., correlations with specific symptoms as well as general severity scores. Details of the unimodal and multimodal analyses are provided in the Statistical Methods section.

### Confidentiality

A dedicated data security concept for this study was developed in close collaboration with the local data protection officer, fully compliant with the EU General Data Protection Regulation [GDPR, Regulation (EU) 2016/679] and the German Federal Data Protection Act (Bundesdatenschutzgesetz, BDSG). The measures ensure both technical and organizational protection of personal data throughout the project. Key provisions include strict pseudonymization and, where feasible, anonymization of all personal data before processing. Access to sensitive data is restricted through a role-based authorization system, and all project staff are trained in privacy and IT security procedures. Data transfers are conducted via encrypted communication channels (TLS/SSL), and stored data is protected using state-of-the-art encryption algorithms. Routine system audits, monitoring, and regular penetration testing are implemented to detect and mitigate vulnerabilities. Redundant backups are encrypted and stored in physically secure environments, with access strictly controlled. Detailed data usage logs and audit trails are maintained to record all data access, modifications, and deletions. The network infrastructure is protected by firewalls and intrusion detection systems, and written informed consent is mandatory for all data subjects. These measures collectively ensure the confidentiality, integrity, and availability of research data, safeguarding data subjects' rights according to EU and German law. Specifically, we implemented the following measures to ensure data security. For every enrolled patient a participation ID will be generated via SecuTrial, a software for managing and conducting clinical trials, offering data collection, management, and analysis with high security and quality standards. One secured document which is saved locally in the University hospital Frankfurt contains the assigned patient identities to the SecuTrial-IDs. All confidential data will be stored exclusively in the university hospital Frankfurt. The questionnaire data will be transferred to SecuTrial and stored under the assigned participant ID. The raw audio files and their transcripts are then pseudonymized by a member of the study group. This involves deleting elements that can be clearly attributed to the patient or the clinician, such as names, addresses, institutions, or other personal information. All files are pseudonymized in compliance with data protection regulations and stored under the assigned participants ID. Password-protected Excel file (256-bit key) with the association of real names is stored in the hospital network. Only designated study personnel with identifiable names have knowledge of this password. Access to the system is logged in a log file.

## Statistical methods

### Statistical methods for primary and secondary outcomes

We will employ a zero-shot prompting approach with OpenAI's recently released GPT-OSS (Generative Pretrained Transformer—Open Source Software) series models, which are available under the permissive Apache 2.0 license and have demonstrated strong performance on reasoning tasks relevant to clinical assessment. We have selected these models for several methodological and practical reasons:

First, their open-weight nature ensures full transparency and reproducibility of our analyses. Second, their mixture-of-experts architecture enables efficient deployment on clinical infrastructure with limited computational resources. Third, their documented performance on complex reasoning tasks, including healthcare-related queries, makes them well-suited for psychiatric assessment applications.

Our primary analytical comparison will involve two model sizes from the GPT-OSS family: GPT-OSS-120B (116.8 billion total parameters with 5.1 billion active parameters per token) and GPT-OSS-20B (20.9 billion total parameters with 3.6 billion active parameters per token) (58). This comparison directly addresses a critical question for clinical deployment: whether larger, more capable models provide sufficient performance advantages to justify their greater computational demands, or whether smaller, more efficient models can achieve comparable diagnostic accuracy. The GPT-OSS-120B model has been shown to achieve near-parity with state-of-the-art reasoning models on standard benchmarks while running efficiently on a single 80GB GPU, whereas GPT-OSS-20B delivers comparable performance to advanced compact models while requiring only 16GB of memory, making it feasible for deployment on standard clinical workstations or even edge devices.

For each model size, we will systematically evaluate two distinct inference configurations defined by the temperature hyperparameter, which controls the randomness of model outputs. We will test a conservative configuration (temperature = 0.1) designed to prioritize consistency and clinical reliability by producing more deterministic responses, and a rather liberal configuration (temperature = 0.8). In the NLP literature the effects of temperature are well represented but systematic clinical applications have yet to be done to our knowledge. Accuracy in multiple choice question answering tasks show high consistency in temperature ranging between 0 and 1, but an expansion to other problem types is recommended (59). This strategic selection of hyperparameters reflects the clinical tension between reproducibility critical for diagnostic applications where consistency across assessments is paramount and the risk of highly inconsistent outcomes that could potentially lead to incorrect diagnoses and treatment recommendations. In addition, we apply top-p (nucleus) sampling with a cumulative probability threshold of 0.9 to each analysis. This setting restricts sampling to the smallest set of tokens whose cumulative probability mass is at least 0.9, balancing output diversity with coherence.

This yields a 2 × 2 factorial design with four experimental conditions: 1. GPT-OSS-120B with temperature 0.1, 2. GPT-OSS-120B with temperature 0.8, 3. GPT-OSS-20B with temperature 0.1, and 4. GPT-OSS-20B with temperature 0.8. We will evaluate each condition's performance on primary outcomes including general diagnostic classification accuracy and suicidality detection, severity score prediction (correlation with standardized clinical measures), and clinical utility metrics such as sensitivity, specificity, and positive/negative predictive values. All model versions, hyperparameters, and inference code will be fully documented and made available to ensure complete reproducibility.

Concurrent with text-based analysis using GPT-OSS models, we will extract acoustic features from therapy session recordings using openSMILE (version 3.0) (56) with the eGeMAPSv02 feature set (60), which includes validated markers known to associate with psychiatric conditions. The eGeMAPSv02 feature set comprises 88 acoustic features encompassing spectral (Mel-frequency cepstral coefficients), glottal (fundamental frequency, jitter, shimmer), and prosodic characteristics (energy, speech rate, voice quality measures such as harmonics-to-noise ratio). These features will be extracted at the frame-level (10-millisecond intervals) and subsequently aggregated using statistical functions (mean, standard deviation, minimum, maximum, percentiles) to produce session-level representations comparable to clinical assessment timeframes.

Our overarching analytical strategy employs a three-tier statistical framework designed to characterize how textual, acoustic, and combined modalities contribute to clinical prediction:
Tier 1: Unimodal Baseline Analysis. We will analyze each modality independently to establish baseline predictive performance before considering fusion. For the text modality, we will conduct two-way mixed-effects logistic regression with outcomes (diagnostic classification or severity degree) regressed on the fixed effects of model size and temperature, with random intercepts for participant and session. Effect sizes will be reported as odds ratios with 95% confidence intervals. For the acoustic modality, we will conduct mixed-effects linear regression using a reduced set of the most clinically relevant acoustic features selected *a priori* based on prior literature associations with depression and suicidality, including pitch variability, energy measures, MFCC and jitter as predictors of continuously scored clinical outcomes (e.g., severity scores from standardized rating scales) (60, 61).Tier 2: Factorial Interaction Analysis for 2 × 2 Design. For text-based predictions, we will formally test the 2 × 2 factorial design using mixed-effects ANOVA to partition variance according to main effects (model size, temperature) and their interaction. Specifically, we will model primary outcome (e.g., predicted depression severity) as a function of fixed effects for model size (GPT-OSS-120B vs. 20B), temperature (0.1 vs. 0.8), and their interaction (Model Size × Temperature), with random intercepts for participants and sessions to account for the hierarchical data structure. This approach allows us to determine whether inference strategy recommendations (conservative vs. liberal temperature) can be applied consistently across model sizes, or whether optimization differs by model choice. If a significant Model Size × Temperature interaction emerges, it would suggest that clinical deployment requires model-specific tuning. Conversely, absence of interaction would support unified recommendations applicable regardless of computational constraints. We will report partial eta-squared (*η*²p) effect sizes with 95% confidence intervals for each factorial term.Tier 3: Multimodal fusion and Late-Fusion Integration. To evaluate how textual and acoustic information combine for clinical prediction, we will employ a structured late-fusion approach. For each of the four 2 × 2 factorial conditions, we will generate separate predictions from the GPT-OSS models (text modality) and from a logistic regression model trained on acoustic features (acoustic modality). We will then integrate these predictions through weighted averaging, with weights determined via cross-validation (80% training, 20% held-out validation) on a stratified subset of sessions. This approach maintains interpretability—each modality's contribution can be quantified—and avoids the architectural complexity that would introduce uncontrolled hyperparameter flexibility incompatible with pre-registration.We will quantify multimodal benefit by comparing fusion performance (AUC, sensitivity/specificity at clinically relevant decision thresholds) against the best unimodal baseline. If fusion provides incremental improvement beyond single modalities, we will use mixed-effects logistic regression with interaction terms to test whether the fusion benefit depends on model size or temperature setting. This tests the hypothesis that acoustic information provides complementary information that enhances text-based predictions uniformly, or whether certain model configurations better leverage multimodal information.

Statistical rigor and assumptions testing. For all mixed-effects models, we will verify assumptions including normality of residuals (Shapiro–Wilk test on standardized residuals), homogeneity of variance (Levene's test), and absence of multicollinearity (variance inflation factors < 5 for predictors). Violations of normality or homogeneity will be addressed through appropriate transformations (e.g., Box-Cox for acoustic features) or robust variance estimation. Missing data will be handled via maximum likelihood estimation under a missing-at-random assumption, standard for mixed-effects models.

Multiple comparisons within the 2 × 2 factorial framework will be controlled via Bonferroni correction applied within each outcome domain (text-based prediction, acoustic baseline, fusion). We will test all fixed effects (model size main effect, temperature main effect, Model Size × Temperature interaction) at *α* = 0.05 (two-tailed). *post-hoc* comparisons between specific factorial cells (e.g., testing whether GPT-OSS-120B at temperature 0.8 outperforms GPT-OSS-20B at temperature 0.1) will be pre-specified and corrected for multiple comparisons.

This simplified, focused approach ensures that our study adheres to pre-registration principles, prevents *post-hoc* methodological flexibility, and provides a reproducible framework that other research groups can directly replicate or build upon.

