### Sample size

To determine the required sample size for comparing the accuracy of our models against the gold standard of a trained psychiatrist's evaluation, we conducted an *a priori* power analysis using G*Power software (43).

We based our effect size estimate on the accuracies reported in previous studies that used machine learning techniques to predict suicidality from clinical data (44). Pestian et al. (45) reported an accuracy of 85%, Bernert et al. (46) reported 90% among 87 studies in their meta-analysis, and Barak-Corren et al. (47) reported 94%. The average accuracy across these studies is 89.2%. Assuming a gold standard accuracy of 100%, we calculated an effect size (Cohen's g) of 0.11 using the formula: g = (P—Po)/√[Po(1—Po)], where *P* is the expected accuracy (0.892) and Po is the gold standard accuracy (1.0).

For our power analysis, we set the following parameters: a two-tailed test, an alpha level of 0.05, a power of 0.80, and a constant proportion of 0.5 (representing a balanced dataset). The results indicated that a total sample size of 162 is required to detect an effect size of 0.11 with 80% power at a significance level of 0.05. The critical values for the lower and upper bounds of the acceptance region are 68 and 94, respectively. The actual power achieved with this sample size is 0.8046757, and the actual alpha level is 0.0491726.

In summary, to compare the accuracy of our models against the gold standard of a trained psychiatrist's evaluation with 80% power and a 5% significance level, we require a total sample size of *n* = 162, assuming an effect size of 0.11 based on the accuracies reported in previous comparable studies. As we expect a drop-out rate of 15%–20% due to technical issues, quality issues etc., we expect to collect *n* = 200 interviews.

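### The only stated sample size and power (n = 162, 80%) are for model accuracy against the psychiatrist reference, not for the 120B-versus-20B comparison that the statistical section calls primary

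*Protocol article*

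**What the plan says.** The Sample size section opens with its purpose: "To determine the required sample size for comparing the accuracy of our models against the gold standard" of a trained psychiatrist's evaluation. Its closing summary repeats that the number is needed "to compare the accuracy of our models against the gold standard of a trained psychiatrist's evaluation with 80% power and a 5% significance level". The result is given as: "The results indicated that a total sample size of 162 is required to detect an effect size of 0.11 with 80% power". This is the only power calculation in the article.

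The section on statistical methods for primary and secondary outcomes names a different contrast: "Our primary analytical comparison will involve two model sizes from the GPT-OSS family", that is, GPT-OSS-120B against GPT-OSS-20B. The question it is meant to answer is "whether larger, more capable models provide sufficient performance advantages to justify their greater computational demands", or whether the smaller model is comparably accurate. Tiers 1 and 2 and the paragraph on statistical rigor test model size, temperature and their interaction as fixed effects in mixed models, with random intercepts for participant and session, at a two-tailed 0.05. Tier 2 also says what a null result would mean: "Conversely, absence of interaction would support unified recommendations applicable regardless of computational constraints".

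Other sections point back to the clinician. Objectives makes suicide-risk assessment and the CGI course the primary aim, with a clinician's assessment as the reference for the AI analysis. Outcomes plans a physician-versus-model comparison, as part of an initial exploratory analysis. Data management repeats the expert reference. The description of the 2 × 2 design lists several primary outcomes to be evaluated in each of four conditions.

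**The concern.** The comparator in the sizing is not the comparator in the analysis labelled primary. The sizing tests one proportion against a constant. The 120B-versus-20B contrast compares two models on the same sessions, so its power depends on how often the two models disagree and in which direction. The article gives no expected difference between the models, no disagreement rate, no margin for comparable accuracy and no power for the interaction.

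Two practical conclusions are at stake: whether the larger model is worth its computing cost, and whether one temperature recommendation can serve both model sizes. The second is to be drawn from the absence of an interaction. A non-significant interaction supports a common recommendation only if the study could have shown a relevant one, and no stated power or interval criterion addresses that.

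**Working it through.** **1. Reproducing the plan's figure.** Inputs from the Sample size section: n = 162, null proportion 0.5, g = 0.11, two-tailed alpha 0.05, critical values 68 and 94. With X ~ Bin(162, p), reject if X ≤ 68 or X ≥ 94.
- Alpha: P(X ≤ 68) + P(X ≥ 94) at p = 0.50 is 0.0491726.
- Power: the same sum at p = 0.50 + 0.11 = 0.61 is 0.8046757.

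Both match the article to every printed digit. The calculation is therefore an exact one-sample test of 0.61 against 0.50. It has no term for model size, temperature or their interaction.

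**2. Does it fit its own stated comparison?** The section says "The average accuracy across these studies is 89.2"% and sets this against a reference accuracy of 100%. The value 0.11 is about 1.0 − 0.892 = 0.108, but the test used it as a distance from 0.5. The printed formula divides by √[Po(1 − Po)], which at Po = 1.0 is √(1.0 × 0) = 0, so it does not yield 0.11 either. The 80% is the power to tell 0.61 from 0.50, not to compare 0.892 with its reference.

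**3. Could 162 be read as a paired sizing?** A sign test at 0.5 is also the form of the McNemar test, but there it counts only discordant sessions. On that reading the total needed would be 162/0.10 = 1,620 sessions at 10% discordance, 162/0.20 = 810 at 20% and 162/0.30 = 540 at 30%. The article plans 200 interviews, and the Sample size section does not describe a paired comparison.

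**4. Illustration for 120B versus 20B.** The article supplies no inputs, so all of these are assumed: 162 independent sessions, one correct/incorrect prediction per model per session, exact McNemar test, two-sided alpha 0.05. Let D be the discordant share and d the accuracy difference. The number of discordant sessions is M ~ Bin(162, D). Given M = m, the number favouring the larger model is Bin(m, (D + d)/(2D)), tested against 0.5. Power is the rejection probability averaged over M.

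Power for an assumed gap of d = 0.05:

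| D | Power |
|---|---|
| 5% (lowest possible for this gap) | about 82% |
| 7% | 61% |
| 8% | 54% |
| 9% | 48% |
| 10% | 44% |
| 15% | 30% |
| 22% | 22% |

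The last row is what independent errors would give at accuracies of 0.90 and 0.85: 0.90 × 0.15 + 0.10 × 0.85 = 0.22.

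The difference detectable with 80% power is about 7 points at D = 10%, 9 points at 15% and 10 points at 20%.

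These figures show how strongly power depends on quantities the sizing does not contain. They are not the power of the planned mixed model.

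**The case against.** The best defence is that 120B versus 20B is not really the trial's primary comparison. Objectives, Outcomes and Data management all centre on model against clinician, the sizing follows that aim, and the model-size contrast may be meant only as the main comparison within the text analysis. The Sample size section also never claims power for model size. This largely stands: a reader might infer that 120B versus 20B is the settled primary and that the study was sized for the wrong question, but the article supports only that its sections disagree. The defence does not remove the disagreement, because the statistical section uses the word primary for the model-size contrast.

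A reader might also infer that the study is underpowered for model size, so that a 5-point advantage would more often be missed than found. The documents do not support this. The 5-point gap and the discordance are assumptions, and power exceeds one half at 8% discordance or less. The plan also runs each model at two temperatures. Averaging over them could raise power, unless the outputs are nearly identical. Repeated sessions per patient could lower it. Tier 2's example outcome is a severity score, to which McNemar figures do not transfer.

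The interaction rule could be called a separate matter of interpretation. It belongs here because it turns a null result into a recommendation that no stated power supports.

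**Conclusion.** The mismatch holds. The n = 162 and 80% power are correct arithmetic for a test of 0.61 against 0.50. They do not apply to the 120B-versus-20B comparison or to the interaction, and the plan to treat absence of interaction as support for common recommendations has no stated power behind it. This conclusion rests on the text and the exact reproduction alone.

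The size of the problem for the model-size contrast cannot be fixed from the article. Under the stated assumptions the detectable difference is about 7–10 points at 10%–20% discordance, and power for a 5-point gap spans about 82% to 22% at 5% to 22% discordance. The planned analysis would give different values.

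It would also go too far to infer that relabelling the reference comparison as primary makes the 80% valid. The calculation does not compare an accuracy of 0.892 with its reference.

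**What to change.** 1. Name one primary comparison and make Objectives, Outcomes, Sample size and the statistical methods section agree on it.
2. In Sample size, state that the 80% power does not cover the model-size or interaction terms. Any detectable difference quoted for model size should carry its assumptions on discordance, independence and number of predictions.
3. In the statistical methods section, report the paired 120B–20B accuracy difference and the Model Size × Temperature interaction with 95% confidence intervals. Replace the rule that absence of interaction supports common recommendations with an interpretation based on the interval.
4. If the reference comparison is named primary, restate its power for the comparison actually intended, with its null value and expected accuracy.

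The cost is wording and a restated calculation. No extra patients, sessions or model runs are needed. The stated assurance on model size and interaction becomes weaker than the present text may suggest.
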